## Methods

### Study protocol

The study involves a parallel group randomised control design to evaluate the potential for activity trackers (Jawbone; Jawbone, Inc. [name]) to be used to provide regular feedback to assist with maintenance of new exercise behaviours following a12-week face to face individualised exercise lifestyle program run by exercise physiologists (Strength2Strength Tasmania Exercise Treatment Initiative). 150 participants who have been referred to the individualised lifestyle program will be recruited for this study. Recruitment will occur through personal invitation at the time of their initial assessment for the lifestyle program. Participants will undergo a suite of tests for variables associated with physical function and clinical prognosis and the beginning and end of the face to face program and at 3, 6 and 12 months of follow-up (Fig. 1). Participants randomised to the activity tracker group will be compared to those who receive usual care and to those who receive telephone counselling, the current best practice for maintenance of lifestyle change.

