### Sample size calculation

The 12 week S2S intervention resulted in a mean increase of 450 MET.min of physical activity per week with a SD of 1.5x the change. Sample size was calculated based on a predicted maintenance of 100% of additional physical activity in the feedback groups and decrease of 50% of additional physical activity in the usual care group over the 12-month intervention (Mean Difference = 225 Met.min/week) with a SD of the change of 350 MET.min/week (1.5x the mean change in line with S2S data). STATA 12 (Statistical data analysis; Stata Corp; College Station; Texas, USA) was used to calculate the sample size on the basis of a mean difference of 225 MET.min/week with a SD of the change of 350 MET.min/week, a power of 80% and an alpha level of 0.05 using the “sampsi 0 225, sd (350) p (0.8) a (0.05)” command. The sample size calculation indicated that at least 38 participants were required per group. To allow for potential withdrawals 50 participants per group will be recruited.

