## Data analysis

All statistical analyses will be performed using STATA statistical software (STATA 13; Statistical data analysis; Stata Corp; College Station; Texas, USA). Baseline and descriptive data between the groups will be analysed with one-way ANOVA. Binary categorical data will be analysed for variability between the groups using logistic regression. Parametric longitudinal data will be analysed using mixed effects linear regression with unstructured covariance, corrected for repeated measures. In the event that assumptions of linear regression (heteroskedascity, skewness, kurtosis or non-linearity) are violated, those analyses will be repeated using repeated measures ordinal logistic regression. *P*-Values will be corrected where appropriate for multiple comparisons using the Holm test. Where participants do not return for follow up or there is missing data, this will be analysed on a last case brought forward basis.

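### The 38 per group is sized for one test at unadjusted alpha 0.05, but the analysis plans a Holm correction; if it covers the arm comparisons, power at 38 is about 68% to 76%, not 80%

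*Protocol article*

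**What the plan says.** The Sample size calculation section uses one two-sample command, "sampsi 0 225, sd (350) p (0.8) a (0.05" (closing bracket not shown), with "a power of 80% and an alpha level of 0.05". The scenario is "predicted maintenance of 100% of additional physical activity in the feedback groups and decrease of 50% of additional physical activity in the usual care group", a difference of 225 MET.min/week. The result is that "at least 38 participants were required per group". The number is raised to 50 to cover withdrawals; no other reason is given.

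The Data analysis section says that P-values "will be corrected where appropriate for multiple comparisons using the Holm test". It does not say which comparisons form the family.

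More than one arm comparison is intended. The Study protocol section says that tracker participants "will be compared to those who receive usual care and to those who receive telephone counselling". The sizing scenario speaks of feedback groups in the plural against usual care, which adds telephone counselling versus usual care.

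**The concern.** A sample size is valid for the test it was computed for. Here the computation is for one pairwise test at 0.05, while the analysis section announces a stricter standard once several comparisons are made. Holm compares its smallest P-value with 0.05/2 when there are two comparisons and with 0.05/3 when there are three. If the correction covers the arm comparisons, the 80% in the sizing section describes a test that will not be the one reported.

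The margin from 38 to 50 does not settle this, because the document has already assigned it to withdrawals. At stake is a moderate loss of power for the main question, and a stated power that a reader cannot tie to the analysis.

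**Working it through.** **Inputs.** Difference 225, SD 350, power 80%, alpha 0.05, 38 required and 50 recruited per group (Sample size calculation). Under the planning scenario the arm means relative to usual care are 0 (usual care), 225 (tracker) and 225 (telephone), so the true tracker-versus-telephone difference is 0. Sidedness is not stated; two-sided is inferred because it reproduces 38, whereas one-sided gives 30.

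**Step 1: reproduce the plan's figure.** n = 2(z₀.₉₇₅ + z₀.₈₀)² × SD² / difference² = 2 × (1.960 + 0.842)² × 350² / 225² = 37.98, so 38. The figure reproduces exactly with no multiplicity allowance.

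**Step 2: lower bound under Holm.** At 38 per group the standardised difference is 225 / (350 × √(2/38)) = 2.802.
- Alpha 0.05: Φ(2.802 − 1.960) = 80.0%
- Alpha 0.05/2: Φ(2.802 − 2.241) = 71%
- Alpha 0.05/3: Φ(2.802 − 2.394) = 66%

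These are first-step (Bonferroni) values. Holm does better because its later steps are less strict, so the full procedure must be simulated.

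**Step 3: full procedure at 38 per group.** Simulation with normal data, pooled variance and t-tests, 300,000 runs. Power is for each feedback-versus-usual-care test unless stated.

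| Procedure | Each test | Both feedback arms |
|---|---|---|
| Unadjusted | 79% | – |
| Holm, two feedback-versus-usual-care tests | 76% | 67% |
| Holm, tracker vs usual care and tracker vs telephone | 70% (tracker vs usual care) | – |
| Holm, all three pairs | 68% | 56% |
| Joint 2-df test at 0.05, then pairwise at 0.05 | 75% | 67% |

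Treating the SD as known, as the plan's formula does, moves these up by about a point: 80% unadjusted, and 77% and 69% for Holm over two feedback-versus-usual-care tests and over three pairs.

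**Step 4: evaluable number for 80%.** Full Holm needs about 42 per group for the two feedback-versus-usual-care tests and about 48 for three pairs. From 50 recruited, that tolerates a loss of 1 − 42/50 = 16% or 1 − 48/50 = 4%. The plan's own margin corresponds to 1 − 38/50 = 24%. With all 50 analysed, three-pair Holm gives about 81% for each test.

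**Step 5: why the joint test suffices with three arms.** If any two of the three pairwise nulls are true, all three means are equal. Every intersection in the closed family is therefore the global null, which the 2-df joint test covers at 0.05. Pairwise tests at 0.05 after a significant joint test then keep strong familywise control. Under the global null at 38 per group, simulated familywise error is 5.0%, against 4.4% for three-pair Holm.

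**The case against.** Four points deserve weight.

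**The family is not stated.** Holm is to be applied only as appropriate, and could be meant for time points or secondary outcomes. A condensed article may leave the family to the full protocol or the SAP. This stands against any claim that the plan corrects all three pairs. It does not remove the mismatch: both the sizing alpha and a multiplicity correction are stated in this document, and each arm family examined falls below 80% at 38.

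**The trial recruits 50, not 38.** A reader might infer that 80% power cannot be delivered. The document does not support that: three-pair Holm reaches about 81% if all 50 are analysed. The article also carries last values forward, which may keep the analysed number near 50. However, nothing in it supports a difference of 225 and SD of 350 for carried-forward values, and the margin is assigned to withdrawals.

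**Power could mean at least one success.** The chance that at least one feedback arm beats usual care is about 80% at 38 even under three-pair Holm. That is true, but the sizing section defines power for a single pairwise contrast.

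**Holm is a valid method.** It controls familywise error, and choosing a less powerful valid method is not an error. The joint-test route is no general free gain. Against Holm on the two feedback-versus-usual-care tests it gives 75% versus 76% at 38. If one arm has half the effect (means 0, 225, 112.5), it gives 68% versus 71% for the stronger arm. It helps only when all three pairs are in the family.

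**Conclusion.** The concern holds as a conditional mismatch. If Holm covers the arm comparisons, the stated 80% at 38 per group becomes about 76%, 70% or 68%, depending on the family. The loss is roughly 3 to 12 points against the stated 80% or the simulated 79%. Whether the trial falls short in practice depends on having at least about 42 or 48 evaluable per group.

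Two further inferences should be avoided. One is that the trial needs 46 or 51 evaluable per group: those are the Bonferroni first-step sizes, and Holm needs fewer. The other is that two primary measures enlarge the family. The abstract lists both accelerometry and the survey, but Physical activity measurement makes the ActivPal data primary and the questionnaire a back-up.

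The result assumes a two-sided test, equal effects in both feedback arms, and the SD of 350 as stated; whether that SD is right is a separate question.

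**What to change.** Name the primary arm comparisons that form the Holm family, and restate the power for that procedure at the expected evaluable number per group. No extra enrolment is needed for this.

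- **If all three pairs are in the family:** replace plain Holm for the arm comparisons with a 2-df joint test of arm at 0.05, followed, only if it is significant, by each pairwise test at 0.05. At 38 per group this gives about 75% each and 67% for both feedback arms, against 68% and 56%. It is still below 80%, so the power must be restated either way.
- **If only the two feedback-versus-usual-care tests are primary:** keep Holm and state about 76% at 38, or 80% at about 42 evaluable.

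The cost is a few sentences and a slightly lower stated power.

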## Discussion

The objective of this trial is to determine the effect of different modalities of ongoing feedback regarding physical activity on the maintenance of activity levels post completion of a 12-week individualised lifestyle program and; the effect of ongoing physical activity levels on a range of health risk factors and health services usage. Due to the ageing and increasingly inactive global population, sustainable and cost effective measures to assist older adults to maintain an increased level of activity need to be put in place. The effectiveness of telephone counselling on behaviour change has been well documented [11, 12] however it is time consuming and expensive when continued over a prolonged period of time. In contrast the effectiveness of remote feedback devices on compliance to prescribed physical activity have not been investigated. The results of this study will help to determine the efficacy of remote physical activity monitoring and feedback devices on compliance to prescribed physical activity compared to the current gold standard of telephone counselling. If the remote monitoring and feedback proves effective, it may provide a cost efficient alternative method of assisting maintenance of behaviour change from lifestyle interventions.
